### Experimental conditions

Upon arrival to the laboratory, pre-experimental monitoring measures will be collected (e.g. physical activity and diet diary) and height measured. Participants will arrive at GIH in a taxi (organised by GIH) to be consistent with energy expenditure and physical activity behaviour. Weight will be measured on the day of the high-nitrate breakfast condition. This day was chosen since nitrate provided will be individualised based on body weight. The participants will perform a practice test of the working memory cognitive task, provide a saliva sample (to assess nitrate/nitrite levels), and be asked to answer questions related to psychological factors (mood, alertness, and sleepiness) before the experimental breakfast conditions (**Fig 2**). The three experimental conditions of this study are as follows:

No breakfastLow-nitrate breakfast (regular breakfast)High-nitrate breakfast (regular breakfast supplemented with nitrate provided through concentrated beetroot juice)

**Fig 2 pone.0285581.g002:**
[figure not shown]
Timeline of measurements and experimental conditions. WM = working memory; fNIRS = functional near-infrared spectroscopy.

On the first breakfast test-day (either condition B or C), participants will be able to choose how much food they want to consume from the foods provided. Foods will include: wholemeal bread, cheese, ham, cucumber, yoghurt, and muesli with low sugar content. On subsequent visits the same and exact amount of food (breakfast will be weighed and documented) will be given to the participants. The breakfast consumption should be as close to the participant’s habitual diet as possible, hence why participants can choose the amount of breakfast that they deem will satisfy them. The breakfast provided will be the same in both breakfast conditions and will not contain foods that have a high glycaemic index (e.g. white bread), to reduce the effects of glucose. Previous research has indicated that postprandial blood glucose concentrations could mediate the effects of breakfast on cognitive function [33]. However, a small amount of orange juice will be provided in both breakfast conditions; primarily to help wash down the taste of the concentrated beetroot juice in the high-nitrate breakfast condition. Participants are allowed to drink water ad libitum throughout the course of each experimental day; however, amounts of fluid will be attempted to be matched for each experimental condition. The amount of nitrate provided in the high-nitrate breakfast condition will be adjusted for weight of the participant and they will be asked to drink all the concentrated beetroot juice. Each 60 ml concentrated beetroot juice shot (product of Umara AB, Sweden) contains 500 mg of nitrate. The amount of nitrate provided will be based on the daily acceptable limit of 3.7 mg per kg body weight per day [50], so for a 40 kg individual the amount of nitrate would be 148 mg. In the scenario that the participant does not consume all the beetroot juice, then the amount they consumed will be documented. There should be very little variation in nitrate content between the shots as they are designed to contain 500 mg of nitrate per 60 ml of concentrated beetroot juice and are all taken from the same batch.

There will be an 80-minute sitting period between the first and second measurements of working memory, cognitive task-related CBF, and arterial stiffness (**Fig 2**). In other words, 130 min from breakfast to the last measurement. The period was determined based on previous research in adults showing that plasma nitrite from beetroot juice peaks at 2.5–3 hrs after ingestion [5]. During the sitting period participants will be able to read books or listen to audio books that can be related to their schoolwork but will not be allowed to use any technological devices nor partake in any physical activity that could lead to arousal. One social break will be provided on each test day, at the same time each test day, whereby the participant can talk to one of the researchers for a duration of 2–3 minutes, which will be consistent for each participant.

### Outcome measures

**Primary outcome:** Working memory.

**Secondary outcomes:** Cognitive task-related CBF, arterial stiffness, psychological factors (mood, alertness, and sleepiness), and salivary nitrate/nitrite concentrations.

#### Working memory

N-back paradigms will be used to assess working memory performance, consisting of the 1-, 2-, and 3-back tests [51] at two time points (time points 1 and 2) after the breakfast experimental conditions (**Fig 2**). The n-back paradigms are computerised numerical versions where the participants will indicate if the digit presented on the screen is the same digit that was presented 1 digit earlier (1-back), 2 digits earlier (2-back), or 3 digits earlier (3-back) (**Fig 3**). Participants will indicate this via a key press within a 2000 ms period from the onset of the digit, whereby each digit is presented for 1500 ms with an inter-stimuli interval of 500 ms. E-Prime 2.0 (Psychology Software Tools) was used to create the n-back tests and for capturing the data. Before each n-back test, participants will be required to stare at a white dot on a black screen and count from zero to reduce mind-wandering for 20 secs, which will be used as the baseline. Average reaction time (m/s) of correct responses and accuracy (number of correct responses) will be measured for each n-back test across the 3 blocks of 20-digit sequences each, with each n-back test lasting 35 secs.

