#### Cerebral blood flow (CBF)

Cognitive task-related CBF will be measured as changes in oxy-Hb and deoxy-Hb via near-infrared light using a non-invasive, multi-channel, continuous wave fNIRS instrument (portable NIRSport, 8–8 system, with short-separation channels, NIRx Medizintechnik GmbH, Berlin, Germany). CBF parameters will be measured at two time points (time points 1 and 2) during the working memory tasks (**Fig 2**). The optodes for this instrument will be placed over the prefrontal cortex and data will be sampled at 7.81 Hz at wavelengths 760 nm and 850 nm. The fNIRS cap has 16 channels created by 8 LED light sources and 8 detectors that are placed according to the standard 10–20 system, with a source-detector separation distance of 3 cm for long-separation channels. Additional short-separation channels with a distance of 0.8 cm, to account for physiological confounders [53], will also be used. CBF was chosen to be measured in the prefrontal cortex because working memory tests such as the n-back tasks have been shown in previous studies to mainly involve this region [53–55]. NIRStar 15.2 software will be used with a predefined montage (Heiland et al. [52] Additional file 2) to record the CBF data during the working memory tasks.

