#### Cerebral blood flow analysis

The task-related relative changes (Δμmol) in oxy-Hb and deoxy-Hb will be estimated using MATLAB-based software NIRS Brain AnalyzIR Toolbox (https://github.com/huppertt/nirs-toolbox [67]). Oxy-Hb will be the predominant cerebral blood flow outcome as it has previously been reported to be the most sensitive indicator of neural activation [68]. FNIRS probe registration will be individualised to account for anatomical differences and probe placement, by using head circumference, nasion-inion, and pre-auricular distances from each participant. Quality check of each signal will be initially performed, including checking the relative coefficient of variation (CV%) for each channel. A CV% less than 15% will indicate good signal quality. Poor signal quality will be dealt with in the statistical analysis. Raw voltage will then be converted to optical density and subsequently to haemoglobin concentrations based on the modified Beer-Lambert law [52]. Data will be processed and analysed in a similar manner outlined in Heiland et al. [52]. Minimal manipulation will be performed on the signals as suggested by Santosa et al. [67]. First level statistics will involve estimating the fNIRS parameters during the 1-, 2-, and 3-back tasks (each 35 sec duration) relative to the baseline (20 sec rest). Brain activation will be predicted using a general linear model (GLM) with a canonical design matrix and an autoregressive pre-whitening approach with iteratively reweighted least squares (AR-IRLS) for each source-detector pair. The AR-IRLS approach will be used because it reduces the false-discovery rate [69]. Short-separation regressors will be used to control for type I errors caused by systemic physiology and motion artefacts. The GLM will yield regression coefficients (betas) for each channel in each n-back task and condition that will be used in the second-level analyses (group-level analysis). This will entail the coefficients of Δoxy- and Δdeoxy-Hb each being averaged across the prefrontal region, and separately by left and right prefrontal hemispheres for each n-back task and condition. A False Discovery Rate (FDR) correction using a Benjamini-Hochberg procedure will be used to correct for multiple comparisons (*q-value* = FDR-adjusted *p ≤ 0*.*05*). Linear mixed effect models will be employed with Δoxy- and Δdeoxy-Hb as dependent variables, with condition and time as fixed effects and subject as a random effect to assess within and between condition differences in CBF parameters comparing the n-back tasks. Linear mixed effects models with maximum likelihood estimation will help to deal with potential missing data. Number of missing data will also be reported and checked for missing data mechanisms. Additional, linear mixed models will be performed to assess intervention effects including time and condition as interaction terms.

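### The n-back timing contradicts itself: the stated digit timing gives 40 s blocks, but the protocol states 35 s and repeats it for the first-level fNIRS model

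*Protocol article*

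**What the plan says.** Two sections of the protocol article fix the timing of the task.

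- **Outcome measures, Working memory.** On the digit cycle: "each digit is presented for 1500 ms with an inter-stimuli interval of 500 ms". Participants respond by "key press within a 2000 ms period from the onset of the digit", which fits a 2 s cycle. Reaction time and accuracy are taken "across the 3 blocks of 20-digit sequences each, with each n-back test lasting 35 secs". Before each test there is a fixation period in which participants "count from zero to reduce mind-wandering for 20 secs, which will be used as the baseline".
- **Statistical methods, Cerebral blood flow analysis.** The first-level step estimates the fNIRS parameters "during the 1-, 2-, and 3-back tasks (each 35 sec duration) relative to the baseline (20 sec rest"). The model is a "general linear model (GLM) with a canonical design matrix and an autoregressive pre-whitening approach". Its betas go forward to the group-level mixed models.

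The article does not say whether block durations in the design matrix are typed in as a constant or read from recorded event markers. The schematic of the task (Fig 3) is not available in the text reviewed.

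**The concern.** Digit count, digit timing and block duration are linked by simple multiplication, and the three stated values do not agree. The 35 s figure appears twice, the second time in the description of the analysis that produces every oxy-Hb and deoxy-Hb estimate.

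A first-level fNIRS model compares the signal during modelled task periods with everything not modelled as task. If the modelled block ends before the real one, the end of the task response falls into the reference level, the intercept rises, and the task betas fall. That would affect cognitive task-related CBF, a secondary outcome, and with it the question of whether CBF changes explain any effect on working memory. A reader also cannot reproduce the task or the design matrix from the text as it stands.

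**Working it through.** **Step 1. Try to reproduce 35 s.** Inputs, all from the Working memory section: 20 digits per block, 1.5 s per digit, 0.5 s interval, 3 blocks.

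| Reading | Arithmetic | Duration |
|---|---|---|
| Every digit followed by an interval | 20 × (1.5 + 0.5) | 40 s |
| No interval after the last digit | 20 × 1.5 + 19 × 0.5 | 39.5 s |
| 19 cycles | 19 × 2.0 | 38 s |
| Interval contained in the 1500 ms | 20 × 1.5 | 30 s |
| All three blocks counted as one test | 3 × 40 | 120 s |

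None gives 35 s. Working backwards, 35 s would need 35 / 2 = 17.5 digits, or a cycle of 35 / 20 = 1.75 s. The plain reading exceeds the stated figure by 40 − 35 = 5 s, which is 5 / 35 = 14% of the stated duration.

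**Step 2. What follows if 40 s blocks are modelled as 35 s.** From the documents: the sampling rate ("data will be sampled at 7.81 Hz at wavelengths 760 nm and 850 nm"), 20 s rest before each block, and three loads in a fixed order. Assumed: a double-gamma response (gamma with shape 6 minus one sixth of gamma with shape 16), no noise, ordinary least squares with an intercept, and true amplitudes of 1, 1.5 and 2 for the 1-, 2- and 3-back. Entries are fitted beta divided by true amplitude.

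| True / modelled block | Rounds of the three loads | 1-back | 2-back | 3-back | Intercept (true value 0) |
|---|---|---|---|---|---|
| 40 s / 35 s | 1 | 0.82 | 0.89 | 0.92 | 0.20 |
| 40 s / 35 s | 3 | 0.79 | 0.87 | 0.91 | 0.23 |
| 35 s / 35 s | 1 or 3 | 1.00 | 1.00 | 1.00 | 0 |
| 40 s / 40 s | 1 or 3 | 1.00 | 1.00 | 1.00 | 0 |
| 35 s / 40 s | 1 | 0.96 | 0.94 | 0.93 | −0.06 |
| 35 s / 40 s | 3 | 0.97 | 0.94 | 0.93 | −0.07 |

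The loss under ordinary least squares is therefore roughly 9 to 20% (8 to 21% at the extremes). With equal amplitudes and three rounds, all loads are attenuated alike, to 0.87. The spread across loads thus comes from the assumed amplitudes. The order of the blocks makes no material difference.

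**Step 3. Sensitivity to pre-whitening.** The protocol specifies autoregressive pre-whitening, not ordinary least squares. Applying a first-order autoregressive filter to both sides moves the ratios for 40 s modelled as 35 s to about 0.68–0.90, the low end arising with strong autocorrelation. The loss could then reach about 30%. The robust reweighting step was not simulated.

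**Step 4. Effect on comparisons.**
- *Between breakfast conditions.* Multiplying all true responses by 1.2 gives fitted betas exactly 1.20 times as large, because the fit is linear in the signal. Equal responses give equal betas. A true proportional difference keeps its ratio but shrinks in absolute size: for the 1-back with three rounds, a true difference of 0.20 becomes 0.20 × 0.79 = 0.16.
- *Between loads.* With three rounds the fitted betas are 1 × 0.7914 = 0.79, 1.5 × 0.8675 = 1.30 and 2 × 0.9055 = 1.81. The steps are 0.51 against a true 0.50, so differences between loads are nearly kept, but the 3-back to 1-back ratio rises from 2.0 to 1.811 / 0.7914 = 2.29.

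**The case against.** The strongest objection is that the inconsistency is one of description and that no bias has been shown. Attenuation needs two facts together: the program runs 40 s blocks, and the design matrix uses 35 s. The documents establish neither. The 35 s in the analysis section is a parenthesis describing the task, and durations may already come from recorded markers. This stands, and it is why the bias must be stated as conditional. It does not remove the point, since a plan followed to the letter, with 20 digits at the stated timing and a 35 s task period, would produce exactly this mismatch. Nor could the missing figure make both text values true.

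Three stronger readings may tempt a reader, and the documents do not support them:

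- **That the breakfast comparisons are invalid.** Every condition and time point uses the same task, and the Discussion says the order of loads is kept. The error would act alike in all conditions. It could cost absolute effect size but would not produce a difference where responses are the same.
- **That the primary outcome is compromised.** Accuracy is defined as a count of correct responses, and no denominator is stated that could be wrong. All participants and conditions receive the same task whichever duration is right, so comparisons of counts are unaffected.
- **That the percentages above estimate the bias in this trial.** They depend on an assumed response shape, assumed amplitudes, the number of rounds and the noise model, and are illustrations only.

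**Conclusion.** The point holds as an internal contradiction with a conditional consequence. The arithmetic is certain: the stated digit timing gives 40 s (39.5 s at the least generous count of intervals), and the protocol states 35 s in two places.

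What follows depends on which figure is wrong:

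- **Blocks run 40 s and are modelled as 35 s.** The last 5 s of each block are treated as rest and the oxy-Hb and deoxy-Hb betas are attenuated, by the illustrative amounts given above. Activation relative to rest, ratios between loads, and the absolute size of condition differences suffer.
- **Blocks last 35 s and are modelled as 35 s.** The betas are recovered exactly, and the error lies in the digit count or digit timing.
- **Durations come from event triggers.** The betas are sound whichever figure is wrong, and only the text needs correction.

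It would go too far to infer that the activation estimates are biased as a matter of fact. Any consequence falls on a secondary outcome. Because a figure tied to the analysis cannot be right alongside the stated task, and the repair is almost free, it should be settled before the fNIRS data are modelled.

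**What to change.** 1. Read the digit count, presentation time, interval and block length from the E-Prime program. Correct whichever is wrong, in both the Working memory and the Cerebral blood flow analysis sections.
2. Say whether a test means one 20-digit block or all three blocks of a load.
3. State that block onsets and durations in the first-level design matrix are taken from the recorded event triggers rather than a fixed 35 s. Replacing 35 s by 40 s without checking is not safe: blocks that truly last 35 s but are modelled as 40 s also give betas that are too small (ratios 0.93 to 0.97).

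The cost is a check of the task program, text corrections in two sections and, if a constant is in use, a small change to how the design matrix is built. Testing of participants does not change. If any fNIRS data have already been modelled with a wrong fixed duration, the first-level step would need to be rerun.

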**Fig 3 pone.0285581.g003:**
[figure not shown]
Schematic of the working memory tasks to measure cognitive function. Adapted from Heiland et al., 2022 [52]. ISI = inter-stimulus interval.

#### Cerebral blood flow (CBF)

Cognitive task-related CBF will be measured as changes in oxy-Hb and deoxy-Hb via near-infrared light using a non-invasive, multi-channel, continuous wave fNIRS instrument (portable NIRSport, 8–8 system, with short-separation channels, NIRx Medizintechnik GmbH, Berlin, Germany). CBF parameters will be measured at two time points (time points 1 and 2) during the working memory tasks (**Fig 2**). The optodes for this instrument will be placed over the prefrontal cortex and data will be sampled at 7.81 Hz at wavelengths 760 nm and 850 nm. The fNIRS cap has 16 channels created by 8 LED light sources and 8 detectors that are placed according to the standard 10–20 system, with a source-detector separation distance of 3 cm for long-separation channels. Additional short-separation channels with a distance of 0.8 cm, to account for physiological confounders [53], will also be used. CBF was chosen to be measured in the prefrontal cortex because working memory tests such as the n-back tasks have been shown in previous studies to mainly involve this region [53–55]. NIRStar 15.2 software will be used with a predefined montage (Heiland et al. [52] Additional file 2) to record the CBF data during the working memory tasks.

After placing the fNIRS cap on the participant’s head, its symmetrical placement will be ascertained by visually ensuring that the Cz point is centrally located and that the distance between the nasion and the Fpz point are aligned. The cap will then be snuggly closed using the chinstrap. System calibration will be performed prior to the cognitive task, after dimming the test room lights to reduce the effects of ambient light, to optimise signal quality. If signal quality is low, then the positioning of the optodes that form the faulty channels will be corrected by moving hair with a cotton swab and/or gel, or the cap will be totally removed and replaced, with subsequent recalibration. After calibration, at time point 1, a mark will be placed on the forehead of the participant just below the cap edge to ensure replicability in the placement of the cap for time point 2. To minimise the auditory distractions while performing the cognitive task, headphones will be recommended to the participant at the initial measurement and subsequently used or not in accordance with the first measurement occasion for consistency. FNIRS signals will be visually inspected for quality, lost channels, and motion artefacts during measurements and any divergences noted.

#### Psychological factors

Psychological factors will be assessed while participants are relaxed and seated and will occur before the experimental conditions (**Fig 2. Time point 0**) and at two subsequent time points (**Fig 2. Time points 1 and 2**). Participants’ mood will be recorded using the Positive and Negative Affect Scale (PANAS) [56]. PANAS has been validated in adolescents and is shown to be a reliable measure of moods [57], with 10 positive and 10 negative moods. Participants will rate their mood on a 5-point scale (very slightly/not at all; a little; moderately; quite a bit; extremely) and will represent how they feel at that moment. The positive affects include: interested, excited, strong, enthusiastic, proud, alert, inspired, determined, attentive, and active; while the negative affects include: distressed, upset, hostile, irritable, scared, jittery, afraid, ashamed, guilty, and nervous. Scores for the positive affects will be added up; providing one overall value and ranging from 10–50 with higher scores indicating higher positive mood. Scores for the negative affects will be added up; providing one overall score and ranging from 10–50 with higher scores indicating more negative mood [56]. Alertness will be measured using a 10 cm visual analogue scale (VAS); ranging from “not at all” to “completely alert” [58]. VAS has previously shown high reliability and validity among adults [59], and also among adolescents [60, 61]. A highly valid measure of sleepiness, the Karolinska Sleepiness Scale questionnaire (KSS) [62, 63], will be used to assess levels of sleepiness via a 9-point Likert scale, ranging from “extremely alert” to “very sleepy, great effort to keep awake, fighting to sleep”; with higher scores indicating higher levels of sleepiness.

#### Arterial stiffness

Arterial stiffness will be measured via two variables: pulse wave velocity (PWV) and augmentation index (AIx) using SphygmoCor XCEL PWA/PWV system [64] at two time points (time points 1 and 2) after the experimental conditions (**Fig 2**). The SphygmoCor XCEL PWA/PWV system has been tested for validity in this age group [65]. While AIx is an indirect measure of arterial stiffness, PWV is considered to be the gold standard [52]. AIx is defined as the difference between the first and second systolic peak and is expressed as a percentage of the pulse pressure. A similar procedure was performed in an earlier study of adolescents [52]. After 2 min of rest, pulse wave analysis (PWA) will be estimated from a brachial arm cuff where blood pressure and waveforms will be derived. This will be followed by measuring PWV from three high fidelity pressure waveforms using a carotid tonometer with a right leg cuff. PWV will be assessed between carotid and femoral arteries and is calculated by the formula: PWV (m/s) = distance between measurement location (m) / transit time (s) [30]. The average of the three recordings will be used to determine PWV (m/s) [66].

